### Participation timeline

2.9

#### Baseline (day 0)

2.9.1

Achieve written informed consent form all patients.Check all inclusion/exclusion criteria.Record demographic information, medical records, cardiovascular risk factors.Perform and record physical examination and 12-lead ECG.Laboratory analysis (CBC, routine biochemistry, inflammatory biomarkers, acute adhesion molecules).2D TTE/speckle tracking.

#### Visit 1 (day 7 / discharge from the hospital)

2.9.2

hs-CRP assessment

#### Visit 2 (month 1)

2.9.3

Angio-CT (coronary plaque vulnerability features assessment, epicardial fat, myocardial perfusion).LGE-CMR (myocardial fibrosis/scar, remodeling, viability).Dobutamine stress echocardiography/speckle tracking (viability).

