The major aim of the urgent revascularization in ST-elevation myocardial infarction (STEMI) is to save myocardial tissue from death and necrosis, in order to recover viable myocardium. Despite a timely revascularization of the epicardial culprit coronary artery, a significant proportion of patients do not present the typical signs for a successful reperfusion, this being defined as the no-reflow phenomenon. Various mechanisms have been incriminated in an attempt to provide an explanation for this phenomenon, including microvascular embolization, endothelial dysfunction due to an exaggerated inflammatory response, or reperfusion injury. The consequences of this phenomenon are expansion of the infarct size, life-threatening arrhythmias, early development of CHF, and enhanced ventricular remodeling and dilation. Diagnosis of no-reflow can be achieved in the catheterization laboratory, during the revascularization procedure, or via imaging techniques such as gadolinium contrast magnetic resonance, contrast echocardiography or nuclear imaging.^[13–16]^

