It is well-known that one of the major factors that trigger an AMI is the systemic inflammation, which has a direct influence on coronary plaque vulnerability.^[17]^ Atheromatous plaques develop and progress due to a chronic non-resolving inflammatory process that occurs at the site of an endothelial injury caused by turbulent blood flow. The atherosclerotic lesions can evolve in a silent manner for a number of years without causing an acute event.^[18]^ However, some plaques become unstable by acquiring several phenotypic changes (large necrotic core, thin cap fibroatheroma, microcalcifications, vascular remodeling) which make them prone to rupture.^[19,20]^ Several studies have shown that vulnerable plaques are associated with an enhanced inflammatory response, which causes overexpression of the vulnerability features, with consequent rupture and thrombosis.^[20–22]^ Furthermore, myocardial injury triggers an inflammatory cascade, which is persistent during the first 3 to 5 days following the acute event, having a benefic reparatory effect.^[23]^ The persistence of an elevated systemic inflammation after AMI after day 3 to 5 has deleterious effects, stimulating the process of left ventricular remodeling and evolution towards CHF. Moreover, the enhanced inflammation secondary to myocardial ischemia, may lead to vulnerabilization of additional atherosclerotic plaques thorough the vascular system, which might explain increased rates of acute coronary and cerebrovascular events in patients that have already suffered an AMI.^[8,24,25]^

The exact influence of various pathophysiological mechanisms, such as no-reflow phenomenon or increased inflammatory response on a pan-coronary level, on the process of ventricular remodeling is not fully understood. Understanding the complex heterogenous interaction of these components could help to identify patients at a higher risk for developing heart failure, as well as subsequent coronary and cerebrovascular events, after they have already suffered an AMI.

The present manuscript describes the procedures of the VIABILITY trial, a descriptive prospective single-center cohort study which intends the assessment of the link between systemic inflammation, pan-coronary plaque vulnerability (referring to the plaque vulnerability within the entire coronary tree), myocardial viability and ventricular remodeling in patients who had suffered a recent STEMI.

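### No-reflow is named beside inflammation as a mechanism of heart failure and remodeling, but it has no defined readout and no adjusted analysis, so it may confound the hs-CRP comparison

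*Protocol article*

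**What the plan says.** **Rationale (section 1.1).** No-reflow appears with enhanced inflammation in the list of predictors of heart failure after infarction. Its stated consequences include "early development of CHF, and enhanced ventricular remodeling and dilation". Its possible causes include microvascular embolization and "endothelial dysfunction due to an exaggerated inflammatory response, or reperfusion injury". On detection, the text says: "Diagnosis of no-reflow can be achieved in the catheterization laboratory, during the revascularization procedure"; it also names gadolinium magnetic resonance, contrast echocardiography and nuclear imaging. The knowledge gap is then put as the influence of mechanisms "such as no-reflow phenomenon or increased inflammatory response on a pan-coronary level, on the process of ventricular remodeling is not fully understood", followed by: "Understanding the complex heterogenous interaction of these components could help to identify patients at a higher risk for developing heart failure".

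**Measurements (sections 2.6 and 2.9).** At baseline the plan is to "Record demographic information, medical records, cardiovascular risk factors", with a physical examination, ECG, laboratory tests and echocardiography. No flow or reperfusion variable from the index procedure is listed. At month 1 the CMR entry is "LGE-CMR (myocardial fibrosis/scar, remodeling, viability", and the CT entry covers plaque features, epicardial fat and myocardial perfusion. Neither is described as a measure of no-reflow.

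**Comparison (sections 2.5, 2.8 and 2.11).** Groups are formed by hs-CRP at day 7, with a cut at 3 mg/dl. The primary outcome is post-infarction heart failure, through readmission or an ejection fraction below 45%. The tests named are Pearson chi-square, Student and Mann-Whitney. No covariate model is mentioned.

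**The concern.** The first secondary objective (section 1.2) is the effect of systemic inflammation on left ventricular remodeling, and the conclusions speak of the consequences of the inflammatory response. Those are causal aims pursued in non-randomized groups. By the document's own account, no-reflow leads to the same outcomes and is linked to inflammation. It also arises at the index procedure, before the day-7 hs-CRP that defines the groups.

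If the high hs-CRP group contains more patients with poor microvascular reperfusion, the planned comparison mixes two mechanisms. Without a recorded no-reflow variable, the mixture cannot be separated afterwards either. A reader of the results could then not tell whether persistent inflammation, or the poor reperfusion that preceded it, accounts for a difference in heart failure or ventricular dilation.

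**Working it through.** **Step 1: is there a readout?** The sections compare as follows.

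| Section | Content | No-reflow defined? |
|---|---|---|
| 1.1 | Predictor of heart failure, cause of remodeling, diagnosable at the procedure | Discussed as a mechanism |
| 1.2 | Objectives | No |
| 2.6, 2.9.6 | Laboratory, ECG, echo, CMR, CT | No |
| 2.8 | Outcomes | No |
| 2.9.1 | Baseline items | No |
| 2.9.3 | CMR and CT at month 1 | Suitable modalities, but no such readout |
| 2.11 | Unadjusted tests | No covariate named |

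**Step 2: how large could the distortion be?** The plan gives no figure on this point to reproduce. Every input below is an assumption except the 50 per group, which comes from section 2.10.

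Let u0 and u1 be the prevalence of no-reflow in the low and high hs-CRP groups, and R the heart-failure risk ratio for no-reflow. Suppose inflammation has no effect of its own. The observed risk ratio between hs-CRP groups is then

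RR = [1 + u1(R − 1)] / [1 + u0(R − 1)].

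| u0 vs u1 | R = 1.5 | R = 2 | R = 3 |
|---|---|---|---|
| 20% vs 20% | 1.00 | 1.00 | 1.00 |
| 15% vs 25% | 1.125/1.075 = 1.05 | 1.25/1.15 = 1.09 | 1.50/1.30 = 1.15 |
| 10% vs 30% | 1.15/1.05 = 1.10 | 1.30/1.10 = 1.18 | 1.60/1.20 = 1.33 |
| 10% vs 40% | 1.20/1.05 = 1.14 | 1.40/1.10 = 1.27 | 1.80/1.20 = 1.50 |

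A second set of assumed values, with heart-failure risk 50% with no-reflow and 20% without (R = 2.5), agrees:

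- At 35% vs 15% prevalence, the high group's rate is 0.35 × 0.50 + 0.65 × 0.20 = 30.5% and the low group's is 0.15 × 0.50 + 0.85 × 0.20 = 24.5%, a ratio of 1.24.
- At 50% vs 10%, the rates are 35% and 23%, a ratio of 1.52.

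**Step 3: chance of a false finding.** Take a heart-failure risk of 15% without no-reflow, 50 per group and a two-sided 5% test (normal approximation, pooled variance under the null).

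- Worst cell (R = 3, 10% vs 40%): the rates are 0.15 × 1.20 = 18% and 0.15 × 1.80 = 27%. The pooled rate is 22.5%. The null standard error is √(2 × 0.225 × 0.775 / 50) = 0.0835, and the alternative standard error is √((0.18 × 0.82 + 0.27 × 0.73) / 50) = 0.0830. The probability of a significant result in the harmful direction is Φ((0.09 − 1.96 × 0.0835) / 0.0830) = Φ(−0.89), about 19%.
- Mildest unequal cell (R = 1.5, 15% vs 25%): about 3%.
- Equal prevalence: the nominal 2.5%.

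The same logic applies to ventricular volumes, but the document gives nothing from which to illustrate a size.

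**The case against.** The strongest reply has four parts.

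**Nothing is promised.** A reader might infer from section 1.1 that the study undertakes to analyse how no-reflow and inflammation interact. The text does not support that. It says such understanding could help identify patients at risk, and neither the objectives nor the outcomes mention no-reflow. This part stands: the point is a gap in control of confounding, not a broken commitment.

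**The data may exist.** A reader might also infer that nothing scheduled could show no-reflow. That is too strong. Gadolinium CMR and CT perfusion are planned at month 1, medical records are collected at baseline, and a condensed article may leave form fields and covariates to fuller documents. What remains is that the article is specific about its readouts and tests, and none of them defines no-reflow.

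**No-reflow may be a mediator.** Section 1.1 gives exaggerated inflammation as one of its causes. To that extent its effect belongs to inflammation, and adjustment would remove part of the association under study. This stands for early inflammation. But the exposure that defines the groups is hs-CRP at day 7, which follows the index procedure, and the other listed causes are not inflammatory. For that exposure no-reflow acts mainly as a prior confounder.

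**Other predictors could confound too.** Section 1.1 lists diabetes, age, renal disease, delayed revascularization and more. That is true, and an adjusted analysis could include others. No-reflow is singled out because the rationale pairs it with inflammation and no listed item records it.

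The restriction to successful revascularization of the culprit lesion (section 2.3) does not settle the matter. Section 1.1 says no-reflow occurs despite timely opening of the epicardial artery, and the formal inclusion list in 2.3.1 does not require success.

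**Conclusion.** The point holds in a limited form. The plan names no-reflow as a mechanism alongside inflammation, defines no readout for it, and names only unadjusted comparisons of non-randomized groups. As written, it cannot separate poor reperfusion from the effect of inflammation.

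It would go too far to say that the effect of no-reflow will be credited to inflammation, or that any observed difference is spurious. Bias requires unequal no-reflow prevalence between the hs-CRP groups, and the document says nothing about that prevalence. The spurious risk ratios of 1.00 to about 1.5, and the 3% to 19% chance of a false harmful finding in the unequal-prevalence cases, rest wholly on assumed prevalences and risks and on the premise of no true inflammation effect. The upper ends need an extreme imbalance. With a moderate imbalance of 15% vs 25% the ratio is only 1.05 to 1.15.

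**What to change.** **Section 2.9.1.** Record final flow in the culprit artery from the index angiogram already performed, with myocardial blush grade where the images can be read, and ST-segment resolution where ECGs from before and after the procedure exist. State the definition of no-reflow in the protocol, and classify each patient before the day-7 hs-CRP is known.

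**Section 2.11.** Keep the unadjusted hs-CRP comparison. Add a sensitivity analysis of heart failure and remodeling adjusted for no-reflow, and report both results together. Note that no-reflow may partly reflect early inflammation, so the adjusted result may remove some of that effect.

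**Cost.** A few form fields read from existing records, with no new procedure, and one more parameter in a 100-patient model. Adjusted estimates will be somewhat less precise if heart-failure events are few, which is a reason to label the adjusted result as a sensitivity analysis.

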#### Visit 3,4,5 (month 3,6,9)

2.9.4

Record results of physical exam, medical records, ECG2D TTE

#### Final study visit (month 12)

2.9.5

Record results of physical exam, medical records, ECG2D TTEEnd-point assessment

#### Study procedures

2.9.6

Medical records, physical exam, laboratory analysis (CBC, biochemistry, serum levels of hs-CRP, MMPs, IL6, NT-pro-BNP, adhesion molecules);ECG.TTE with morphological measurements, assessment left ventricular systolic and diastolic performance, speckle tracking echo, Dobutamine viability test.LGE-CMR with the evaluation of myocardial scar and fibrosis, ventricular function and remodeling index.Angio-CT with assessment of coronary plaque vulnerability (based on vulnerability features: positive remodeling, spotty calcification, napkin-ring sign, low-density plaque) and myocardial perfusion.

All study procedures are illustrated in Figure 1, which presents the VIABILITY flowchart.

**Figure 1 F1:**
[figure not shown]
Study flowchart.

### Sample size

2.10

One hundred patients with STEMI who underwent successful revascularization of the culprit lesion within the first 12 hours after the onset of symptoms will be enrolled in this study. On the basis of the persistence of systemic inflammation at 7 days after the acute event patients will be allocated into 2 subgroups. Stat Mate 2.0 software was used in order to establish the sample size of the study. According to this computation, a sample size of 50 subjects per group presents a 90% power to detect an increase in major adverse CV events rates proportion of 3.28, with a significance level (alpha) of 0.05 (2-tailed). Therefore, the study population was established at 100 subjects.

### Statistical analysis

2.11

Graph Pad in Stat 3.10 software (GraphPad Software, San Diego, CA) will be used in order to perform all the statistical analysis, using a level of significance of 5%. Normality tests will be performed in order to check all study data. Categorical variables will be interpreted with Pearson Chi-Square test and being presented as numerical or percentage values respectively. Continuous variables will be presented in the form of a mean value +/- SD and will be compared using the Student test for variables with gaussian distribution and Mann–Whitney test for variable with non-gaussian distribution.

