### Background and rationale

1.1

It is well-known that the highest risk of death following an acute myocardial infarction (AMI) is within the first hours from onset. In the latest years, introduction of coronary care units and large-scale implementation of networks for emergency myocardial revascularization, as well as development of reperfusion and pharmacological therapies, led to a significant decrease in mortality rates following AMI. However, the high incidence of post-infarction heart failure is still affecting the long-term outcomes of these patients.^[1–4]^

Congestive heart failure (CHF) as a long-term complication following AMI, although having a relatively low incidence in the primary percutaneous coronary intervention (PCI) era, is an important predictor of mortality and morbidity, at the same time leading to increased health-care costs and decreased quality of life.^[5]^ Predictors for CHF following an AMI include preexistent heart failure, traditional cardiovascular risk factors (diabetes, hypertension, old age, smoking, chronic renal disease), previous myocardial infarction (MI) with or without revascularization, rhythm disturbances during the acute phase of the coronary event, delayed revascularization times, multivessel coronary artery disease (CAD), enhanced inflammatory response, or no-reflow phenomenon after revascularization.^[6–9]^

Multiple coinciding pathophysiological mechanisms may lead to heart failure after AMI, both during the index event and later on. These include myocardial necrosis and stunning, inflammation, reperfusion injury, microvascular obstruction, fibrosis and remodeling. CHF during the acute phase of an acute coronary syndrome results from a combination of myocardial necrosis and stunning, as well as ischemic (including papillary muscle dysfunction and subsequent mitral regurgitation, cardiac tamponade, ventricular overload) and arrhythmic complications. Later onset of CHF arises as a consequence of myocardial scarring and remodeling.^[5,10–12]^

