### Study objectives

1.2

The *primary objective* consists in the evaluation of the relationship between coronary inflammation-mediated plaque vulnerability, myocardial viability and ventricular remodeling in the post-infarction period.

The *secondary objectives* of the study are:

(1)to assess the effect of systemic inflammation on the structural remodeling process of the left ventricle (LV) following an AMI and(2)to evaluate the impact of local inflammatory response on pan-coronary plaque vulnerability in the post-infarction period.

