### Study design

2.1

VIABILITY is a prospective, non-randomized, cohort study, carried out in a single-center, which aims to assess the link between systemic inflammation, pan-coronary plaque vulnerability (referring to the plaque vulnerability within the entire coronary tree), myocardial viability and ventricular remodeling in patients with recent STEMI.

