### Study population and subgroups

2.5

This study will enroll 100 patients with STEMI meeting the inclusion criteria. Study subjects will be distributed in 2 groups: group 1 – patients with STEMI and increased inflammatory response at 7 days after the acute event (hs-CRP ≥ 3 mg/dl) and group 2 - subjects with STEMI and no increased inflammatory response at 7 days (hs-CRP <3 mg/dl).

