## Conclusions

4

The primary contribution of the VIABILITY trial will be to elucidate the consequence of infarct-related inflammatory response on several major determinants for post-infarction outcomes, such as coronary plaque vulnerability, myocardial viability, and ventricular remodeling.

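### The statistical section states only unadjusted two-group tests for a non-randomised cohort split by day-7 hs-CRP, and no model that relates plaque vulnerability, viability and remodeling

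*Protocol article*

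**What the plan says.** Section 2.1 describes the design: "VIABILITY is a prospective, non-randomized, cohort study, carried out in a single-center". Section 2.5 defines the only two groups in the study, hs-CRP at or above versus below 3 mg/dl at day 7.

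Section 2.11 names one software package that "will be used in order to perform all the statistical analysis" at the 5% level. For categorical data, "Categorical variables will be interpreted with Pearson Chi-Square test". Continuous data are compared by Student's test or Mann-Whitney, depending on normality. The design sections mention no regression, correlation, stratification, matching or covariate adjustment.

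The primary objective in section 1.2 is the "evaluation of the relationship between coronary inflammation-mediated plaque vulnerability, myocardial viability and ventricular remodeling". The two secondary objectives ask for the effect of systemic inflammation on ventricular remodeling and the impact of local inflammation on plaque vulnerability. Section 4 says the trial will "elucidate the consequence of infarct-related inflammatory response on several major determinants for post-infarction outcomes".

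**The concern.** Two things do not fit together.

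- **Confounding.** hs-CRP at day 7 is set by the patient's own disease, not by allocation. Section 1.1 lists predictors of post-infarction heart failure, among them age, diabetes, renal disease and "delayed revascularization times, multivessel coronary artery disease (CAD), enhanced inflammatory response". Inflammation is thus one predictor among many, and the stated tests hold none of the others constant. The most important is infarct severity, which the article links to both inflammation and heart failure.
- **Objective without a matching analysis.** The primary objective concerns three imaging constructs. hs-CRP group is none of the three, and no cut-point on any of them is defined. A comparison by hs-CRP group does not describe how the three vary together.

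At stake is a report that credits inflammation with a difference arising partly or wholly from infarct severity, and a primary objective answered at best by unadjusted pairwise comparisons.

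**Working it through.** Section 2.11 gives no figure to reproduce. The sample size section supplies 50 per group, used below; its effect size of 3.28 plays no part in this point.

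**Step 1: is there a common cause on the document's own account?**

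- Section 1.1: myocardial injury starts an inflammatory cascade, and its persistence beyond days 3 to 5 is harmful. This links injury to the grouping variable.
- Section 3: progression to heart failure is tied directly to the extent of myocardial injury, and infarct size is an independent prognostic factor for heart failure. This links injury to the primary outcome in section 2.8.

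The direction of possible bias is therefore given by the document. The strength of either link is not.

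**Step 2: illustration for a continuous outcome.**

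Assumptions: log hs-CRP, infarct size and outcome are jointly normal; the split is at the median, 50 v 50; hs-CRP has no effect of its own. Infarct size correlates *r* with log hs-CRP and *s* with the outcome.

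- The correlation induced between hs-CRP and outcome is *r* × *s*.
- The means of a standard normal variable above and below its median differ by 2 × √(2/π) = 1.596. The spurious group difference is therefore 1.596 × *r* × *s*, in SD of the outcome.
- The within-group SD is √(1 − (*rs*)² × 2/π), and the t-test's noncentrality is (difference / within-group SD) × √(50/2).

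Worked at the two ends:

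- *r* = 0.3, *s* = 0.4: difference 1.596 × 0.12 = 0.19 SD; noncentrality 0.192 × 5 = 0.96; rejection 16%.
- *r* = 0.5, *s* = 0.6: difference 1.596 × 0.30 = 0.48 SD; within-group SD 0.971; noncentrality 0.493 × 5 = 2.47; rejection 68% to 69%.

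| *r* | *s* | Spurious difference (SD) | t-test rejects (simulated) | Rejects after adjusting for infarct size |
|---|---|---|---|---|
| 0.3 | 0.4 | 0.19 | 16% | 5% |
| 0.3 | 0.6 | 0.29 | 30% | 5% |
| 0.5 | 0.4 | 0.32 | 36% | 5% |
| 0.5 | 0.6 | 0.48 | 68% | 5% |

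Simulation used 5,000 datasets per row. The last column is a best case, because it adjusts for infarct size measured without error.

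**Step 3: illustration for the heart failure outcome.**

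Assumptions: infarcts are large or small; heart failure risk is 30% or 40% after a large infarct and 10% after a small one; hs-CRP has no effect. Group risk = share with large infarct × risk if large + share with small infarct × risk if small.

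- Large infarct in 60% v 40%, risk 30%: 0.6 × 0.3 + 0.4 × 0.1 = 0.22 against 0.4 × 0.3 + 0.6 × 0.1 = 0.18. Ratio 1.22; Pearson chi-square rejects in 8%.
- Large infarct in 80% v 20%, risk 40%: 0.8 × 0.4 + 0.2 × 0.1 = 0.34 against 0.2 × 0.4 + 0.8 × 0.1 = 0.16. Ratio 2.1; rejects in 56%.
- With infarct size balanced, it rejects in about 5%.

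**Step 4: objective against tests.**

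Section 1.2 asks how plaque vulnerability, viability and remodeling relate. Section 2.11 offers tests of one variable between two groups. They can examine one pair at a time if one member is dichotomised, for example scar volume by presence of a CT feature. They cannot describe the three together or hold a confounder constant.

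**The case against.** **The study calls itself descriptive.** The abstract and introduction do so, and they speak of a link. Unadjusted comparison suits description. But the secondary objectives and the conclusions speak of effect, impact and consequence, so the wording has to change with the analysis.

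**A separate analysis plan may hold the models, and the reference to all the analysis is grammatically about software.** This is fair. The point therefore rests on what section 2.11 does state, set against the objectives, not on missing covariate lists. As stated, the methods do not match objectives worded as effects and relationships.

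**The size is assumed.** This stands. A reader might infer that the hs-CRP contrast will be confounded, or that any difference found is only infarct size. The document supports neither: it gives the direction of both links and no strength.

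**The tests are not useless for the primary objective.** This also stands. A reader might infer that no listed test can address it, or that the study will yield no estimate for it. Section 2.11 does not confine its tests to the hs-CRP groups, and scar or volumes could be compared by presence of a napkin-ring sign or spotty calcification. What is absent is a stated joint or adjusted analysis.

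**Pearson's chi-square and few events.** A reader might infer that Pearson's test should give way to Fisher's. Exact enumeration at 50 v 50 does not support this. For event rates from 2% to 20%, Pearson's type I error runs from 1.3% to 5.5% and Fisher's from 0.04% to 2.8%. At assumed rates of 9.84% v 3.0%, power would fall from 26.7% to 12.6%. The document gives no 3% rate; its one figure, a recurrent event in 20% of survivors within 12 months, would mean about 10 events per group of 50.

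**Conclusion.** The point holds in this form: the only stated analyses are unadjusted, the cohort is non-randomised and grouped by a marker that the article ties to myocardial injury, and no stated model relates the three constructs of the primary objective. An unadjusted hs-CRP contrast *can* reflect infarct severity rather than inflammation. Under the assumptions shown, false positive rates run from about 16% to 68% for a continuous outcome and from 8% to 56% for heart failure, against a nominal 5%. These are illustrations, not estimates for this trial: they depend on assumed correlations and risks and on an even split. The mismatch between objectives and tests depends on none of them.

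**What to change.** Prespecify as main analyses:

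1. A linear regression of month-12 left ventricular measures on log hs-CRP as a continuous variable, adjusted for the baseline value and a small set of baseline confounders that are recorded. For the heart failure outcome, use a sparing model with two or three covariates, for example penalised logistic regression.
2. A regression or correlation analysis of remodeling and viability on the CT vulnerable-plaque features, adjusted for the same set.

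LGE scar is measured at month 1, after the day-7 hs-CRP, and may lie on the pathway from inflammation to remodeling. In the hs-CRP models, show results with scar only as a sensitivity analysis. Keep the two-group tests, including Pearson's, as descriptive, and word objectives and conclusions as associations.

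**Cost.** No new patients or visits. Section 2.9 already schedules demographics, risk factors, ECG and echocardiography at baseline, CT and CMR at month 1, and echocardiography at month 12. Time to PCI and multivessel disease are not listed among the recorded baseline items, so their capture should be confirmed before they are named as covariates. One hundred patients support few covariates, above all in the binary model, so some confounding will remain. The software named in section 2.11 may need to be replaced or supplemented.

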#### Biomarkers assays

2.6.1

Routine biochemistry and CBC analysis will be performed at the main laboratory of the Emergency Clinical County Hospital of Tirgu-Mures, immediately after randomization. Inflammatory status (hs-CRP levels) will be evaluated at 7 days after the acute cardiac event via immunoturbidimetric assay. Adhesion molecules (VCAM, ICAM), matrix metalloproteinase 9, and interleukin-6 serum levels will be evaluated using enzyme linked immunosorbent assay. Serum inflammatory biomarkers will be analyzed in Advanced Medical and Pharmaceutical Research Center of the University of Medicine and Pharmacy Tirgu-Mures, Romania. N-terminal prohormone of brain natriuretic peptide (NT-proBNP) levels will be evaluated at randomization and at the last follow-up visit, at the main laboratory of the Emergency Clinical County Hospital of Tirgu-Mures by electrogenerated chemiluminescence.

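### Section 2.11 summarises every continuous variable as mean ± SD, including those it judges non-Gaussian and tests by Mann–Whitney: a minor reporting mismatch that one sentence corrects

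*Protocol article*

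**What the plan says.** Section 2.11 (Statistical analysis) begins with a distribution check: "Normality tests will be performed in order to check all study data". It then sets the presentation rule, "Continuous variables will be presented in the form of a mean value +/- SD", with no exception for variables that fail the check. The test, by contrast, depends on the result. Continuous variables "will be compared using the Student test for variables with gaussian distribution", and the alternative is the "Mann–Whitney test for variable with non-gaussian distribution". The significance level is 5%; section 2.10 specifies it as two-sided.

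Section 2.6.1 (Biomarkers assays) names the serum measurements to which this rule will apply. Besides hs-CRP and NT-proBNP, it lists the adhesion molecules VCAM and ICAM, and states that "matrix metalloproteinase 9, and interleukin-6 serum levels will be evaluated using enzyme linked immunosorbent assay".

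The article nowhere provides a median, interquartile range, geometric mean or log-scale summary for a variable judged non-Gaussian.

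**The concern.** The plan expects some variables to be non-Gaussian and changes the test for them, but keeps a summary suited to roughly symmetric data. Two things follow.

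- **Description.** The variables most likely to be affected are positive concentrations. If they are right-skewed, the mean lies above most patients, and the SD can exceed the mean, which suggests impossible negative values.
- **Reading the p-value.** A table that puts group means beside a Mann–Whitney p-value invites the reader to take the p-value as a statement about those means. Mann–Whitney is sensitive to departures of P(X>Y) from 1/2 and does not compare means. Where the shapes of the two distributions differ, the means and the ranks can tell different stories.

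At stake is how the biomarker comparisons behind the inflammation objectives (section 1.2) are described and read. The tests themselves are not in question.

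**Working it through.** **Inputs.** From the article: mean ± SD for all continuous variables, Student or Mann–Whitney by normality (section 2.11), two-sided 5% level and 50 patients per group (section 2.10). Not in the article: any SD or distribution for the biomarkers. Lognormal data with log-SD s between 0.6 and 1.4 are assumed, for illustration only. The plan states no figure of its own on this point, so there is none to reproduce; its sample-size figure does not bear on it.

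**Step 1: how well mean ± SD describes a skewed variable.** For a lognormal variable with median 1:
- mean/median = exp(s²/2)
- SD/mean = √(exp(s²) − 1)
- share of patients below the mean = Φ(s/2)

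| s | mean/median | SD/mean | mean − SD | share below mean |
|---|---|---|---|---|
| 0.6 | 1.20 | 0.66 | 0.41 | 62% |
| 1.0 | 1.65 | 1.31 | 1.65 − 2.16 = −0.51 | 69% |
| 1.2 | 2.05 | 1.79 | 2.05 − 3.69 = −1.63 | 73% |

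The SD equals the mean when exp(s²) = 2, so s = √(ln 2) = 0.83; above that, mean − SD is negative. This step needs no difference between the groups: it concerns the summary within each group.

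**Step 2: do the means and the Mann–Whitney test agree?** Simulated lognormal data, 50 per group, 4,000 runs per scenario:

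- *Same shape, multiplicative shift* (s = 1.0 in both groups, log shift 0.5): Mann–Whitney is significant in 68% of runs; it is significant with the sample means pointing the other way in 0.3%.
- *Equal medians, unequal spread* (s = 0.6 and 1.2): the mean ratio is exp((1.44 − 0.36)/2) = 1.72, yet Mann–Whitney is significant in only 5.5% of runs.
- *Mean 9% higher, median 36% lower in the group with wider spread* (s = 0.6 and 1.2, log-median difference −0.45): Mann–Whitney is significant in 63% of runs, and in 26% of all runs it is significant while the sample means point the other way.

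So the conflict is close to absent under a shift. It appears when spread differs and the means and medians are arranged in particular ways.

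**Step 3: what a rejection means when the means are equal.** For two lognormals with equal means, the median ratio is exp(−(s₁² − s₂²)/2) and P(X>Y) = Φ(−[(s₁² − s₂²)/2] / √(s₁² + s₂²)).

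| s₁ vs s₂ | median ratio | P(X>Y) | Mann–Whitney rejects, 50/50 | 30/70 |
|---|---|---|---|---|
| 1.0 vs 1.0 | 1.00 | 0.50 | about 5% | about 5% |
| 1.0 vs 0.8 | exp(−0.18) = 0.84 | 0.44 | about 15% | about 14% |
| 1.2 vs 0.8 | exp(−0.40) = 0.67 | 0.39 | about 47% | about 42% |
| 1.4 vs 0.8 | exp(−0.66) = 0.52 | 0.34 | about 79% | about 69% |

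In the last three rows the groups truly differ on the quantity that Mann–Whitney addresses, so these rates are power. In the first row, where the distributions are identical, the rate is nominal.

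**The case against.** The strongest reply is that the tests are sound and only a descriptive column is at issue. Much of this stands.

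- A reader might infer from Step 3 that the plan inflates false positives, since Mann–Whitney rejects far more than 5% of the time when means are equal. The article does not support this. In those scenarios the medians differ by a factor of 0.84, 0.67 or 0.52, and the test is right to detect it. The scenarios also require a wider spread to be exactly offset by a lower median, which nothing in the article suggests.
- A reader might infer that reversed directions will be common. If the true mean difference is set to zero, the sign of the sample means is mostly noise, so frequent disagreement with the medians is built in. Under a same-shape shift it is 0.3%.
- The plan reports group means, not a mean difference. The contrast is one the reader would draw, not an estimate the plan announces. That section 2.11 names no effect estimate or confidence interval is not itself a fault, because an article commonly leaves this to the full protocol or analysis plan.
- Day-7 hs-CRP does not belong in the argument. It defines the two groups at 3 mg/dl (section 2.5), so every value in one group exceeds every value in the other, and means and ranks cannot disagree.
- Skewness of the biomarkers is assumed. The plan does, however, provide for non-Gaussian variables itself.

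The reply does not remove the core. Mean ± SD for variables judged non-Gaussian is a rule that section 2.11 states, not a detail left open, and an analysis plan that followed it would repeat the mismatch.

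**Conclusion.** The point holds as a minor reporting correction. Section 2.11 prescribes mean ± SD for variables that the same sentence treats as non-Gaussian. Under the lognormal assumption with log-SD 1.0, that puts the reported mean at 1.65 times the median and the lower limit below zero; at log-SD 0.6 the distortion is milder (1.20 times, with mean − SD still positive). The p-value beside those means answers a different question, but a practical conflict needs unequal spread and cannot be predicted from the article.

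It would be wrong to conclude that type I error is inflated or that the main results are at risk. The primary outcome (section 2.8) is an incidence, the sample size (section 2.10) rests on event rates, and section 2.11 assigns categorical data to the chi-square test. None of these is affected.

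**What to change.** Amend section 2.11 so that the summary follows the test: mean ± SD for continuous variables compared by the Student test, and median (interquartile range) for those compared by Mann–Whitney. Ideally, add a Hodges–Lehmann shift with 95% CI for the latter, so that an estimate accompanies the p-value. An optional alternative for the serum concentrations, if decided in advance, is to analyse them on the log scale and report geometric mean ratios with 95% CI.

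The cost is one sentence and a few lines of analysis, with no extra patients or data. The downside is that tables no longer share one uniform format, and comparison with papers that report means will need a footnote.
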